### Participant Timeline

Participants referred by MCS will be sent an email from H4C, with brief information about the Hope Programme and the feasibility study. The email will contain a link to a Qualtrics survey that contains digital versions of (1) the participant information sheet (PIS), (2) the consent form, and (3) study questionnaires. The PIS and consent form are included in Multimedia Appendix 2. Participants are explicitly informed that they will be randomly assigned to one of two Hope Programmes, starting either in May or in June. Informed consent will be obtained online in accordance with relevant UK legislation (ie, Data Protection Act 2018). The PIS and consent form must be read and agreed to (eg, by checking relevant boxes) before the participant can proceed to the study questionnaires.

After providing informed consent to take part in the study, all participants will be guided through the process of completing the baseline questionnaires (Time 0; hereafter, T0). Upon completion of T0 questionnaires, participants will be randomized via the Qualtrics randomization function, to either attend the Hope Programme starting in May 2020 (intervention group [IG]) or in June 2020 (wait-list control group [WLCG]). Participants are notified which group they have been randomized to at the end of the survey. There will be approximately 30 participants in each group. The IG will then be sent an email link that provides access to the Hope Programme. Those randomized to the WLCG will be informed that they will receive an email link shortly before the start of the Hope Programme in June (ie, approximately 6 weeks later). After 6 weeks (T1), all participants will be emailed a link to the Qualtrics survey containing the secondary outcome questionnaires, and IG participants will also receive a participant debrief at T1. The debrief contains information reminding the participant why the study is being conducted and what will happen to the results, thanking them for their time, and includes sources of additional support if they experienced any distress through completing the questionnaires, such as their own general practitioner or the Samaritans. The WLCG also receive the survey link via email again, with secondary outcome measures and debrief, after they have received the intervention (T2). Table 1 provides a list of all digital study documents presented to participants at each time point (T0, T1, T2). All information and questionnaires at T0, T1, and T2 will be delivered via the Qualtrics survey platform. The Hope Programme will be delivered via the H4C platform.

**Table 1 table1:** Information and questionnaires presented to IG and WLCG participants at each time point (T0, T1, and T2), across the duration of the study.^a^

Study documents	T0	T1		T2
	IG and WLCG	IG	WLCG	WLCG
Participant information sheet	✓			
Informed consent	✓			
Sociodemographic and health questionnaire	✓			
Warwick Edinburgh Mental Wellbeing Scale	✓	✓	✓	✓
Patient Health Questionnaire	✓	✓	✓	✓
Generalized Anxiety Disorder scale	✓	✓	✓	✓
Patient Activation Measure	✓	✓	✓	✓
Poststudy debrief information		✓		✓

^a^T0 refers to the beginning of the study; T1 is 6 weeks later, after the intervention group (IG) has completed the Hope Programme; T2 is an additional 6 weeks later, after the wait-list control group (WLCG) has completed the Hope Programme.

### Sample Size

Participants for this feasibility RCT were drawn from an opportunity sample, referred by MCS, of people with cancer who had expressed an interest in joining the Hope Programme (N=61). As a feasibility study, it was not necessary to conduct sample size calculations to power the study [40]. An arbitrary sample size of n=40 was deemed appropriate for this feasibility study, informed by similar studies in this area [41].

### Recruitment

We contacted all 61 people with cancer from an opportunity sample of people who expressed interest in attending the in-person MCS Hope Programme and invited them to participate in a trial of the digital program. MCS originally recruited these participants through their social media networks (eg, Macmillan Facebook page and website) and Macmillan Information Centres. Given the urgent need to provide immediate support during the COVID-19 crisis, we did not want to delay the study by seeking National Health Service (NHS) ethics approval to recruit NHS patients. Instead, with University ethics approval in place, we only recruited participants who were recruited via non-NHS sources such as the MCS website and their social media networks. Participant recruitment flow is depicted in Figure 1.

**Figure 1 figure1:**
[figure not shown]
Flow diagram showing participants' route through the study.

### Assignment of Intervention

#### Allocation Sequence Generation

The participants will be randomly assigned to the IG or WLCG using a 1:1 allocation ratio. Randomization and the allocation sequence will be generated automatically on completion of the online consent form and baseline questionnaires, using the randomization function in Qualtrics Survey Software (Qualtrics). The research team will be unable to influence any aspect of the randomization procedure.

#### Allocation Concealment Mechanism

Participants were informed upon completion of the T0 questionnaires, via a notification in Qualtrics, whether they had been randomized to the IG (in this case, starting in May 2020), or the WLCG (in this case, starting in June 2020). The research team remained unaware of participant allocation until group contact lists were created at the next data collection point (ie, T1).

#### Blinding

It will not be possible to “blind” participants to allocation. Analysis of outcome measures will be conducted blind to participant allocation where possible (eg, IG and WLCG data will be arbitrarily renamed “Group A” and “Group B” for the purpose of analysis).

### Data Collection, Management, and Analysis

#### Data Collection Methods

All data will be collected via online questionnaires administered through Qualtrics. The validated questionnaires (PHQ-9, GAD-7, WEMWBS, and PAM) have been described in the section on Objectives above. Participants will be entered into a prize draw to win a £50 Amazon voucher as an incentive to complete all study questionnaires.

#### Data Management

Each participant in this study will have a unique identifier (ID) generated by Qualtrics at enrollment, and this will be used to link participants’ survey data together at the end of the trial. The user engagement and analytics data collected by the Hope platform will be linked to the survey data by the unique ID. The linked survey and analytics data will be prepared initially in Microsoft Excel (Microsoft Corp) format, and will then be exported to IBM SPSS Statistics 26 (Version 26; IBM Corp), cleaned, and checked for missing values (all data will remain within the shared, password-protected project folder). Once the research team agree that all required data is present and complete, all survey data will be permanently deleted from Qualtrics. The complete anonymized research data files will be stored on the research team’s shared, password-protected project folder located on the university server. To comply with UK regulations (ie, General Data Protection Regulation and the Data Protection Act 2018), the research data will be retained for 3 years after the study has ended and will then be deleted. Only members of the research team will have access to the data files.

#### Statistical Methods

Quantitative data will be analyzed descriptively. Measures of mean and variance, including confidence intervals and standard deviations, and number and percent for categorical variables, will be used to describe the full range of data at baseline and postprogram. An intention-to-treat analysis will be incorporated, where missing data will be rectified using the last observation carried forward [42]. Between-group inferential comparisons will not be performed as the study was not designed to be powered for this analysis, in concordance with the CONSORT (Consolidated Standards of Reporting Trials) extension for pilot and feasibility trials [43]. All analyses will be performed using IBM SPSS Statistics 26.

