#### Sample Size and Effect Size Estimation

To inform sample size estimation for a future definitive trial, we will calculate the standard deviations of the continuous secondary outcomes pertaining to depression, anxiety, mental well-being, and participant confidence in managing their cancer. To estimate potential effect sizes for a primary outcome in a future definitive trial (namely, change in scores on key secondary outcome measures from preprogram to postprogram), we will calculate the difference between the mean difference preprogram and postprogram for the intervention and control groups and divide by the pooled standard deviation at baseline [34].

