#### Progression Criteria

We will collate the data from all participants in this feasibility RCT to inform progression to a definitive trial, based on the following criteria:

Recruitment rate >70% of eligible participants consentedQuestionnaire completion rate >70% of participants completing T1 questionnairesProgram completion rate >50% of participants attending all 6 Hope Programme sessions

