#### Harms

Participants who indicate they are feeling suicidal at any point during the study on the PHQ-9 measure will be provided with the contact details of local mental health agencies and Samaritans, and will be encouraged to visit their general practitioner. We will also contact the MCS administrator. At postprogram, all participants’ data will be analyzed to examine if any people have reached a probable clinical level of depression or anxiety where they previously were not at this level. This will be recorded and listed as possible adverse effects of the intervention. These participants will be contacted and encouraged to visit their general practitioner and will be signposted to further sources of support as listed above.

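### Last observation carried forward is baseline carried forward here: every T1 non-completer is scored as zero change, which biases the effect size meant to inform the definitive trial

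*Protocol article*

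**What the plan says.** **Missing data.** Statistical Methods states: "An intention-to-treat analysis will be incorporated, where missing data will be rectified using the last observation carried forward". No other method for missing data is named.

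**Assessment times.** The footnote to Table 1 reads: "T0 refers to the beginning of the study; T1 is 6 weeks later, after the intervention group (IG) has completed the Hope Programme". Table 1 shows no questionnaire between T0 and T1. T2 applies to the wait-list group only, after it has had the programme. On baseline completeness, Participant Timeline says: "Upon completion of T0 questionnaires, participants will be randomized via the Qualtrics randomization function".

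**Use of the data.** Sample Size and Effect Size Estimation gives the numerator of the effect size as "we will calculate the difference between the mean difference preprogram and postprogram for the intervention and control groups" and then says to "divide by the pooled standard deviation at baseline". The same section says "we will calculate the standard deviations of the continuous secondary outcomes", without giving the time point. Objectives lists this estimation among the primary outcomes.

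**Missing T1 data.** Progression Criteria asks for a "completion rate >70% of participants completing T1" questionnaires. Retention and Follow-up Rates accepts that people who do not return the questionnaire may nevertheless have gone through part or the whole of the programme. It adds that their reasons will not be sought.

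**The concern.** Carrying the last observation forward usually means carrying an interim value. There is no interim value here, so for anyone missing T1 the carried value is the T0 score and the change is zero by construction.

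The protocol gives no reason to believe in that zero, and some reasons to doubt it:

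- A non-completer in the intervention group may have done the whole programme.
- Strengths and Limitations suggests that people who open only a few sessions may still get what they came for.
- The Introduction describes mental health deteriorating during lockdown, so no change is not a safe assumption for controls either.
- With no reasons for non-completion collected, the assumption cannot be checked afterwards.

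What is at stake is the planning estimate. The imputed zeros enter the effect-size numerator directly, and that effect size is one of the trial's listed products. The recovery rates defined under Secondary Outcome Measures would be affected in the same way: a T0 case with no T1 stays in the denominator and counts as not recovered.

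**Working it through.** **Is there a figure to reproduce?** No. The target of n=40 is called arbitrary, and about 30 per group is 61/2 = 30.5. The protocol states no expected dropout, effect, SD, T0–T1 correlation, alpha or power. All such values below are assumptions.

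**1. Expected effect size under the rule.** Let g and c be the true mean changes in the intervention (IG) and wait-list (WLCG) arms, in baseline SD units with positive meaning improvement. Let m_IG and m_WLCG be the fractions missing T1, unrelated to outcome. Each missing person contributes zero, so

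effect under LOCF = (1 − m_IG)·g − (1 − m_WLCG)·c.

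With equal missingness m this is (1 − m)(g − c) = (1 − m)·d. A simulation with 400,000 per arm, d = 0.50 and m = 0.30 gave 0.350 under LOCF and 0.501 on observed cases, against 0.35 and 0.50 expected.

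**2. Consequence for a sample size based on the effect alone.** With two-sided 5% alpha, 80% power and 1:1 allocation,

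n per arm = 2(1.96 + 0.842)²/d² ≈ 15.70/d².

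For an assumed true d of 0.40:

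| Missing T1, both arms | Effect under LOCF | n per arm, about | Ratio 1/(1 − m)² |
|---|---|---|---|
| 0% | 0.40 | 98 | 1.00 |
| 10% | 0.36 | 121 | 1.23 |
| 20% | 0.32 | 153 | 1.56 |
| 30% | 0.28 | 200 | 2.04 |

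The ratio does not depend on the assumed d. The last row is the limiting case, because the progression criterion requires more than 70% completion.

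**3. Unequal missingness.** The criterion is not stated by arm, so the arms may differ. Each example below averages 30% missing over equal arms, again the limit.

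- No true effect, shared improvement of 0.3, 40%/20% missing in IG/WLCG: 0.6 × 0.3 − 0.8 × 0.3 = 0.18 − 0.24 = −0.06.
- True effect 0.30 (g = 0.5, c = 0.2), 40%/20% missing: 0.6 × 0.5 − 0.8 × 0.2 = 0.14.
- Same true effect, 10%/50% missing: 0.9 × 0.5 − 0.5 × 0.2 = 0.35.

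The direction of the bias is therefore not fixed.

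**4. Which SDs are affected?** Set the SD to 1 at both times, assume correlation 0.6, and take m = 0.30.

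- Baseline SD: unchanged, because T0 is completed before randomisation.
- Postprogram SD: √(1 + m(1 − m)g²), which is 1.00 for g = 0 and √1.0525 = 1.026 for g = 0.5.
- SD of change: the true value is √(2 × 0.4) = 0.894. Under LOCF it is √(0.7 × 0.8) = 0.748 for g = 0 and √(0.56 + 0.0525) = 0.783 for g = 0.5, about 12–16% too small.
- T0–T1 correlation: 0.7 × 0.6 + 0.3 = 0.72 instead of 0.60.

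**5. Partial offset.** If a planner used both the shrunken effect and the shrunken change SD (d = 0.40, leaving out the small m(1− m)g² term), n per arm would go from 15.70 × 0.80/0.16 ≈ 79 to 15.70 × 0.56/0.0784 ≈ 112. That is a ratio of 1.43, not 2.04.

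**The case against.** The case for leaving the rule alone has real parts.

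- **No decision in this trial depends on it.** The three progression criteria concern consent, T1 completion and attendance, and between-group tests are excluded. This stands as a limit on severity. It does not rescue the effect size, which is a product of the trial in its own right.
- **Sampling error is much larger.** A rough 95% half-width for d is 1.96√(2/n): 0.62 with 20 per arm and 0.51 with 30. The loss of 0.12 at 30% missing lies well inside that. True, but a systematic error that costs little to remove need not be added to the random one.
- **Equal random dropout makes the future trial too large rather than too small.** True for that case only; step 3 shows the other direction.
- **The wording does not make LOCF exclusive.** Statistical Methods says that the analysis will be incorporated, so observed-case results may also be reported. That is possible, but the article does not say so, nor which version feeds the effect size.

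A reader might also infer more than the text supports:

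- **That all the SDs are biased.** The stated denominator is the baseline SD, which is untouched, and the postprogram SD barely moves under random missingness. Only a change-score SD is materially affected, and the protocol does not say that it will use one.
- **That a covariance-adjusted sample size would be understated through an inflated correlation.** No correlation or covariance analysis is planned.
- **That harms will be undercounted.** The Harms section looks for people who have "reached a probable clinical level of depression or anxiety where they previously were not at this level", but does not say that imputed scores are used. Someone without T1 data cannot be identified under any method.
- **That the definitive trial would double in size.** The factor 2.04 is the limiting 30% case, on the effect size alone.

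**Conclusion.** The point holds for the effect size. For T1 in the randomised comparison the named rule is baseline carried forward, and the zero change it assigns is not supported by the protocol's own account of non-completers. The planned effect size is biased unless T1 is complete or the missing changes happen to leave the between-group difference unaltered, as they would if non-completers truly did not change.

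Under equal random missingness the effect shrinks by the fraction missing, so a sample size worked from it alone is inflated by 1.23, 1.56 or 2.04 at 10%, 20% or 30% missing. With unequal missingness and change in both arms the error can have either sign. The baseline SD is unaffected. A change SD or T0–T1 correlation, if one were taken from the filled-in data, would be materially distorted.

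These sizes rest on assumed missingness unrelated to outcome and on assumed values for the true effect, correlation, alpha and power; the protocol gives none. A wait-list participant with T1 but no T2 would have T1 carried forward, but that lies outside the randomised comparison.

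**What to change.** In Statistical Methods, replace the carried-forward rule for the main estimates:

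- Compute the effect size, any SD of change and the recovery rates from observed T1 data, with all randomised participants who have T1 kept in their allocated arm. Alternatively, use a method valid under missing at random, such as a mixed model or multiple imputation that includes baseline. For a deliberately descriptive study the observed-data version is enough.
- Report the number and percentage missing T1 by arm beside each estimate.
- In Sample Size and Effect Size Estimation, say which time point or change the SDs refer to.
- Keep last observation carried forward, if at all, as a sensitivity analysis labelled as baseline carried forward.

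The cost is about a paragraph of wording and a few lines of analysis code, with no new data. Intervals will be somewhat wider, and the estimates will rest on a missing-at-random assumption (a stronger form of it for the simple observed-data version) that the trial cannot test, since reasons for non-completion are not collected.

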### Monitoring

#### Data Monitoring

In this small feasibility trial, it was not deemed necessary to employ an independent data monitoring committee. However, participant data was screened at T0, T1, and T2 by the research team to check for indications of suicidal thoughts on the PHQ-9 questionnaire.

#### Harms

Participants who indicate they are feeling suicidal at any point during the study on the PHQ-9 measure will be provided with the contact details of local mental health agencies and Samaritans, and will be encouraged to visit their general practitioner. We will also contact the MCS administrator. At postprogram, all participants’ data will be analyzed to examine if any people have reached a probable clinical level of depression or anxiety where they previously were not at this level. This will be recorded and listed as possible adverse effects of the intervention. These participants will be contacted and encouraged to visit their general practitioner and will be signposted to further sources of support as listed above.

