### Secondary Outcome Measures

We will administer a sociodemographic and health questionnaire at baseline only, requesting the following personal information from participants: gender, age, ethnicity, marital status, highest level of education, employment and occupation, and some details about their cancer diagnosis and any other medical conditions.

Participants will complete a set of validated questionnaires preprogram and postprogram, to give an indication of changes in depression, anxiety, mental well-being, and confidence to self-manage their cancer across the intervention and control groups. These questionnaires are detailed below.

The Patient Health Questionnaire (PHQ-9) [35] is a 9-item measure that assesses the frequency of depression symptoms (eg, “over the past two weeks, how often have you been bothered by any of the following problems … i) little interest or pleasure in doing things; ii) feeling down, depressed or hopeless; iii) poor appetite or overeating”). Responses to each of the 9 items range from 0 to 3 (0=not at all, 1=several days, 2=more than half the days, 3=nearly every day), leading to a summed score between 0-27, with higher scores indicating greater severity of depression. Scores of ≥10 are presumed to be above the clinical range, and so scores of ≥10 are classed as “cases” of depression. Recovery rates are calculated as those patients who score ≥10 (cases) prior to treatment and <10 posttreatment.

The Generalized Anxiety Disorder scale (GAD-7) [36] is a 7-item scale measuring symptoms of generalized anxiety disorder (eg, “Over the past two weeks, how often have you been bothered by the following problems … i) feeling nervous, anxious or on edge; ii) trouble relaxing; iii) becoming easily annoyed or irritable”). Responses to all 7 items range from 0 to 3 (0=not at all, 1=several days, 2=more than half the days, 3=nearly every day), providing a total score of 0-21, with higher scores indicating greater anxiety. Scores of ≥8 are classed as “cases” of generalized anxiety disorder. Recovery rates are calculated as those patients who score ≥8 (cases) prior to treatment and <8 posttreatment.

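### The harm rule counts only new crossings of a caseness cut-off, so worsening in baseline cases goes unrecorded on that scale, and the wait-list T1 data have no stated comparator role

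*Protocol article*

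**What the plan says.** The Harms section has two strands.

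- **Suicidality.** The first concerns "Participants who indicate they are feeling suicidal at any point during the study on the PHQ-9 measure". They are given sources of help and the charity's administrator is contacted. Data Monitoring places this screen at T0, T1 and T2. Neither section says that a positive screen is recorded as an adverse effect.
- **New caseness.** At postprogram the data of all participants are examined to see "if any people have reached a probable clinical level of depression or anxiety where they previously were not at this level". The section then states: "This will be recorded and listed as possible adverse effects of the intervention". These people are also contacted and signposted.

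Harms does not define the clinical level. Secondary Outcome Measures supplies the only candidates: for the PHQ-9, "scores of ≥10 are classed as “cases” of depression", and for the GAD-7, "Scores of ≥8 are classed as “cases” of generalized anxiety disorder". That section also defines recovery for people who start as cases, but gives no matching rule for deterioration.

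Under Participant Timeline and Table 1, both arms complete the PHQ-9 and GAD-7 at T0 and T1. The wait-list arm completes them again at T2, six weeks after T1, once it has had the programme.

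**The concern.** The rule is stated, so the point is not about detail left to an analysis plan. It has three weaknesses.

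1. **It is blind to worsening from above the cut-off.** A PHQ-9 move from 9 to 10 is listed and a move from 10 to 27 is not. The most symptomatic participants can be recorded as recovering but not as deteriorating on that scale.
2. **The list has no stated reference rate.** Some people near a cut-off will cross it in six weeks whatever they receive. The wait-list arm at T1 measures that rate over the same weeks of the pandemic, yet Harms does not say it will be set beside the intervention count.
3. **The time point is open for the wait-list arm.** Crossings that arise during the wait could enter a list headed as possible effects of an intervention those people had not yet received.

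The trial is meant to inform a definitive one, so a harms summary that is hard to read may carry forward.

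**Working it through.** The plan states no harm rate, so there is no figure to reproduce. The check has two parts.

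**A. The time point**

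- Sample Size and Effect Size Estimation contrasts preprogram-to-postprogram change between arms. For the wait-list arm that makes sense only if postprogram means T1.
- The footnote to Table 1 places the wait-list arm's completion of the programme at T2. The Results section ends postprogram collection in August 2020, which fits the inclusion of T2.
- If postprogram means T1, wait-list crossings are pre-exposure. If it means T2 and the reference is T0, the window is 6 + 6 = 12 weeks, half of it unexposed, and a crossing during the wait that persists would still be listed. Only a T1-to-T2 comparison isolates the exposed period, and the text does not specify it.

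**B. Size of the two effects (illustration)**

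From the document: PHQ-9 cut-off 10, GAD-7 cut-off 8, about 30 participants per arm.

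Assumed, not from the document: scores bivariate normal with the same mean and SD at both times (no true change); PHQ-9 mean 6 to 10, SD 5 to 6, correlation r of 0.6 to 0.8. The cut-off is taken at 9.5 because scores are integers.

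With z = (9.5 − mean)/SD, Φ the normal distribution function and Φ₂ the bivariate one:

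- P(case at T0) = 1 − Φ(z)
- P(new case at T1, of all participants) = Φ(z) − Φ₂(z, z; r)

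| Mean | SD | r | z | Case at T0 | New case at T1 | Per 30 |
|---|---|---|---|---|---|---|
| 6 | 5 | 0.8 | 0.70 | 0.242 | 0.758 − 0.679 = 0.079 | 2.4 |
| 8 | 5 | 0.7 | 0.30 | 0.382 | 0.618 − 0.497 = 0.121 | 3.6 |
| 10 | 5 | 0.6 | −0.10 | 0.540 | 0.460 − 0.313 = 0.147 | 4.4 |

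Over the whole grid, new crossings run from 7.9% to 14.7% of participants and baseline cases from 24% to 54%. The same means, SDs and correlations with the GAD-7 cut-off at 7.5 give 9.0% to 14.7% and 38% to 69%.

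A separate simulation used rounded scores clipped to the scale range, PHQ-9 means of 7 to 11, GAD-7 means of 6 to 10, SD 5 to 6 and r of 0.5 to 0.8. It gave new crossings of about 9% to 17% on each scale, or roughly 3 to 5 per 30. In the same simulation, 0.3 to 2.5 baseline cases per 30 rose by 5 points or more with no true change and would go uncounted. The 5 points serve only to illustrate.

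At a crossing rate of 10%, P(at least one in 30) = 1 − 0.9³⁰ = 0.96. Under these assumptions, an intervention-arm list with entries is close to certain even if the programme does nothing.

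**The case against.** The other side has several good points.

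- **Causality is not asserted.** The list is of possible effects. Recording candidate events before judging cause is ordinary safety practice. A reader might infer that the trial would report false harm; the text does not support that.
- **The control arm is not ignored.** All participants' data are examined, and Blinding has the outcomes analysed as two labelled groups. A reader might infer that wait-list data go unused. What the text supports is narrower: they have no stated comparator role for harms.
- **Baseline cases have partial cover.** The suicidality screen reaches them, and a case on one scale can newly cross on the other. It would be too strong to say they have no way to register worsening. But the screen reads suicidal responses, not overall worsening, and is not said to be recorded as an adverse effect.
- **Carry-forward.** Statistical Methods says "missing data will be rectified using the last observation carried forward", and a reader might infer that dropouts are thereby scored as unharmed. That sentence concerns the intention-to-treat analysis; nothing says imputed scores feed the harm check. Nor would the inference always hold: a wait-list participant who crossed at T1 and missed T2 would carry the crossing forward.
- **Small arms cannot settle causality.** With an assumed 20 non-cases per arm and a 15% rate, the 95% half-width for the difference is 1.96 × √(2 × 0.15 × 0.85 / 20) = 0.22. This rules out making the label of possible effect conditional on a comparison with the wait-list rate. It does not argue against showing the counts.

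The gap for baseline cases, the missing comparator role and the open time point remain.

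**Conclusion.** The point holds in limited form. As written, the rule cannot record worsening on a scale where the participant was already a case at T0. It gives the concurrent unexposed data no stated role in reading the list, and it leaves open whether pre-exposure wait-list crossings are listed as possible intervention effects.

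These follow from the text, taking the clinical level to mean the document's own case cut-offs. The sizes do not: 8% to 15% crossing by fluctuation and 24% to 54% baseline cases on the PHQ-9 rest wholly on assumed means, SDs and correlations with no true change.

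No primary feasibility outcome or progression criterion depends on the rule. The weight is minor to moderate, and the case for acting is mainly that the change is cheap.

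**What to change.** Leave the individual listing and the contact with participants exactly as they are. State which time points define the check for the wait-list arm, and add one descriptive table by randomised arm, for each scale:

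1. New caseness from T0 to T1. The denominator is participants who were non-cases at T0 with an observed T1 score. Show missing T1 separately and use no carried-forward scores.
2. Participants whose score rises from T0 to T1 by a prespecified amount, whatever their T0 status. The trial team should set and justify the amount, since the document offers none.
3. Wait-list events from T1 to T2, shown separately as post-exposure.

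Read the list alongside the wait-list T1 count, without making an entry depend on it. Any interval on the difference should be labelled descriptive, in keeping with the exclusion of between-group inference in Statistical Methods.

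The cost is one table from data already collected.
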